## **11. REPORTING ADVERSE EVENTS**

All unexpected and serious adverse events which may be due to study treatment or intervention must be reported to the FHCRC Institutional Review Office as soon as possible but within at least 7 calendar days of the investigator learning of the event.

### **11.1 Definition of an Adverse Event**

Any untoward medical occurrence in a patient or clinical investigation subject administered a pharmaceutical product, medical treatment or procedure and which does not necessarily have to have a causal relationship with this treatment.

#### **1. Life-threatening Adverse Event**

Any adverse event that places the patient or subject, in view of the investigator, at immediate risk of death from the reaction.

#### **2. Unexpected Adverse Event**

An unexpected adverse event is an adverse event that is not described in the study protocol or informed consent.

#### **3. Serious Adverse Event (SAE)**

Any adverse event occurring that results in any of the following outcomes:

- death,
- a life-threatening adverse event (real risk of dying),
- inpatient hospitalization or prolongation of existing hospitalization,
- a persistent or significant disability/incapacity,
- a congenital anomaly
- requires intervention to prevent permanent impairment of damage.

### **11.2 Attribution -**

- Related – includes adverse events that are definitely, probably, or possibly related to the medical treatment or procedure.
- Not Related – includes adverse events are doubtfully related or clearly not related to the medical treatment or procedure.

### **11.3 Procedure for Reporting Adverse Events**

The FHCRC Serious Adverse Event (SAE) Report Form will be completed for all adverse events that meet the expedited reporting requirements. The SAE form will be faxed to the IRO at [contact]. All available information should be submitted but it is acceptable to fax an incomplete report form at the initial report. A completed report should be faxed as soon as possible but must be received within 15 calendar days.

Serious adverse events that do not meet the requirement for expedited reporting (not related to study treatment or expected) must be reported to the IRB as part of the annual renewal of the protocol.

## **12. STATISTICAL CONSIDERATIONS**

### **12.1. Sample Size**

The sample size of this clinical trials is modest but sufficiently powerful to fulfill the primary goal of this proposal – determine if prior lymphodepletion extends the survival

Protocol 1796.00

of transferred antigen-specific CD8+ T cell clones. The major immunologic endpoint, in vivo survival of transferred T cells was used to determine patient sample size.

For each patient, the T cell survival of infused CD8+ CTL given alone (Infusion #1) will be compared with subsequent infusion (Infusion #2) given with prior fludarabine conditioning. Since the second infusion given occurs 2 weeks after the first infusion at a time when transferred CD8 cells have disappeared from the circulation, residual cells from the first infusion will not be a confounding factor since, in our previous study, transferred CD8+ T cells were undetectable at two weeks.

Statistical modeling indicates that, with a sample size of 12 patients, and assumed true difference in T cell survival with fludarabine conditioning compared to infusions without of at least 4 days with a standard deviation (SD) of 2 days, we shall have approximately 99% power to detect a statistically significant difference in T cell survival at the two-sided level of significance of .05 (one-sample t-test). These power estimates do not depend on the actual assumed-true values, rather only on the difference between the values. The design of this trial using the first infusion of CD8 T cells administered alone as a baseline for each patient permits intra-patient analysis using paired samples with increased statistical power.

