#### **2.4.6. Use of Interleukin-2 in Adoptive T Cell Therapy**

Analysis of T cell persistence following 22 infusions of CD8+ T cell clones without IL-2 demonstrated a pattern of T cell survival characterized by an average increase in T cell frequency on Day 1, from  $< 1/20,000$  to  $1/480$  PBMCs or  $> 1\%$  of all CD8+ T cells, followed by a steady rapid decline to  $1/1500$  by Day 7 and  $< 1/20,000$  by Day 14. The median survival of CD8+ T cells given without IL-2 was  $6.56 \pm 0.82$  days. To extend the period of in vivo persistence, the study was modified to include four unmodified T cell infusions three weeks apart, the 2nd, 3rd and 4th infusions being accompanied by a 14-day course of low-dose IL-2 following each infusion (at doses of 0.25, 0.50 and 1.0 MU/  $m^2$  s.c. twice daily). These doses are 50- fold less than the high doses of IL-2 administered for the treatment of melanoma, do not mediate the toxicity associated with high-dose infusions, and by itself, has no anti-melanoma effect. Analysis of T cell persistence from 12 infusions of CD8+ T cell clones given with low-dose IL-2 demonstrated a pattern of T cell survival characterized by an increase in frequency to  $1/490$  PBMCs or  $> 1\%$  CD8+ cells in the peripheral blood on Day 1 that was sustained at an average of  $1/890$  PBMCs until Day 14 at which time, IL-2 was discontinued and T cell frequency fell to  $< 1/5700$  by Day 21. The average median survival of CD8+ T cells following an infusion of T cells with IL-2 was  $16.78 \pm 1.6$  days which was significantly longer than that observed in infusions administered to the same patient without IL-2.

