### **2.6 Initial Results from Protocol 1796 "Fludarabine Lymphodepletion in Adoptive T Cell Therapy"**

Four patients have been treated on Protocol 1796 on the original protocol which included the administration of fludarabine as a lymphodepleting agent before the second T cell infusion but no inclusion of IL-2 with either the 1st or 2nd infusion. As of June, 2004, analysis of the data after treating the first 4 patients on this study has demonstrated that:

1. there are no safety concerns (i.e., no serious adverse events)
2. in vivo persistence was prolonged slightly from median of 7 to 23 days

This increase is less than expected given the anticipation that prior lymphodepletion resulting in increased serum IL-7 and IL-15 levels would result in survival for several weeks and even in vivo expansion which was not observed in the clinical trial. In fact, the increase is only slightly increased compared to a 2 week course of low-dose IL-2 (median survival of 16.9 days). Published studies performed in murine models demonstrate that even with prior depletion (e.g. with cytoxan), CD8 T cell persistence may not be prolonged unless IL-2 is also given. In this case, the use of fludarabine also ablated any potential CD4 help from the peripheral blood and, alone, did not appear to be sufficient to provide prolonged in vivo persistence. Based on these observations and previously published studies using other lymphodepleting agents in combination with IL-2, low-dose IL-2 (at a dose previously shown to be safe and effective in prolonging T cell survival in vivo) will be incorporated into the design of the study. In this study, a 14-day course of low-dose IL-2 following both the first and second T cell infusions will be administered. Since fludarabine lymphodepletion precedes only the second T cell infusion, any differences in T cell survival can be attributed to lymphodepletion alone.

Protocol 1796.00

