|                             | Day +7                               | x                            |                                | x                     | x              | x                 | x           |                                |
|                             | Day+ 14                              | x                            |                                | x                     | x              | x                 | x           |                                |
| Pre-infusion
Fludarabine | Day +21                              | x                            | IV placement
Administer FLU | x                     | x              | x                 | x           |                                |
| Pre-infusion
Fludarabine | Day +22                              | x                            | IV placement
Administer FLU |                       | x              |                   |             |                                |
| Pre-infusion
Fludarabine | Day +23                              | x                            | IV placement
Administer FLU |                       | x              |                   | x           |                                |
| Pre-infusion
Fludarabine | Day +24                              | x                            | IV placement
Administer FLU |                       | x              |                   |             |                                |
| Pre-infusion
Fludarabine | Day +25                              | x                            | IV placement
Administer FLU |                       | x              |                   | x           |                                |
|                             | Day +26                              |                              |                                |                       | x              |                   |             |                                |
|                             | Day +27                              |                              |                                |                       | x              |                   |             |                                |
| INFUSION #2          | Day+ 28
Pre-Infusion             | x                            | IV placement                   | x                     | x              | x                 | x           |                                |

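### Section 12.1 rules out carry-over with a 2-week gap and no-IL-2 clearance data that conflict with the rest of the protocol, and Section 2.6 credits the contrast to lymphodepletion alone

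*Protocol*

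**What the plan says.** Section 12.1 compares T cell survival within each patient between Infusion #1, described as cells without any accompanying treatment, and Infusion #2 after fludarabine. It states that residual cells will not confound the comparison, for two reasons: "Since the second infusion given occurs 2 weeks after the first infusion at a time when transferred CD8 cells have disappeared from the circulation", and in the previous study "transferred CD8+ T cells were undetectable at two weeks".

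Other parts of the protocol read differently:

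- Appendix D has Infusion #1 on Day 0, fludarabine on Days +21 to +25, and Infusion #2 at "Day+ 28 Pre-Infusion". Section 7.2 starts fludarabine 7 days before Infusion #2, which agrees with Appendix D (28 − 7 = 21).
- Section 2.6 explains that the first four patients were treated without IL-2 and that a 14-day low-dose course now follows both infusions. It concludes that "any differences in T cell survival can be attributed to lymphodepletion alone".
- Section 2.4.6 gives the earlier clearance data separately for infusions without and with IL-2. With IL-2, cells were sustained until Day 14, "at which time, IL-2 was discontinued and T cell frequency fell to" below 1/5700 by Day 21.
- Section 4 uses with-IL-2 figures (median about 17 days; below 0.1% of CD8+ cells at 21 days). Section 7.2 still uses no-IL-2 figures (median under 7 days; below 0.1% at 14 days).

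**The concern.** Persistence without and with fludarabine is a primary objective (Section 3.1.2) and is the endpoint that set the sample size. The comparison is sound only if cells from Infusion #1 are not counted in the persistence of Infusion #2. Section 12.1 offers one safeguard, namely that the first cells have gone, and supports it with an interval and clearance data that do not match the regimen described elsewhere. If residual cells were present at Infusion #2, they would add to its measured persistence and favour fludarabine.

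The attribution sentence in Section 2.6 has a related weakness. Giving IL-2 after both infusions removes IL-2 as a difference between them. But the study is nonrandomized and fludarabine always precedes the second infusion. Infusion #2 therefore also differs in following an earlier infusion and an earlier IL-2 course, and in coming later in the disease.

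**Working it through.** **1. The plan's own power figure.** Section 12.1 specifies a two-sided 0.05 one-sample t-test "with a sample size of 12 patients", with a true difference "of at least 4 days with a standard deviation (SD) of 2 days". It does not say whether the SD is that of the paired difference or of a single infusion. Power comes from the noncentral t distribution with 11 degrees of freedom and noncentrality difference/SD × √n.

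- SD of the difference = 2: noncentrality 4/2 × √12 = 6.93; power above 0.999.
- SD of 2 per infusion, uncorrelated: SD of the difference 2 × √2 = 2.83; noncentrality 4/2.83 × √12 = 4.90; power 0.993.

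Both readings support the stated figure of about 99%. Neither depends on the interval between infusions.

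**2. Clearance data (Section 2.4.6, fraction of PBMCs).**

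| | Day 1 | Later | Last value | Median survival |
|---|---|---|---|---|
| Without IL-2 (22 infusions) | 1/480 | 1/1500 at Day 7 | <1/20,000 at Day 14 | 6.56 days |
| With IL-2 (12 infusions) | 1/490 | average 1/890 until Day 14 | <1/5700 at Day 21 | 16.78 days |

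The claim of no detectable cells at two weeks matches only the first row. In the second row, the average up to Day 14 is 20,000/890 = 22 times the 1/20,000 bound. The median survival of 16.78 days is longer than the 14-day gap on which Section 12.1 relies. The Day 21 bound is 20,000/5700 = 3.5 times the 1/20,000 bound, so it does not show that cells are undetectable.

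**3. What might remain at Day 28.** The protocol gives no with-IL-2 value for Day 28. Taking the Day 21 upper bound and assuming exponential decline with half-life h, the Day 28 level is at most 1/(5700 × 2^(7/h)).

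| Assumed h (days) | Source of the assumption | Day 28, at most about | Share of Day 1 level (1/490) |
|---|---|---|---|
| 2.6 | 7 ln 2 / ln(5700/890) | 1/36,500 | 490/36,500 = 1.3% |
| 3.65 | no-IL-2 fall, 6 ln 2 / ln(1500/480) | 1/21,500 | 490/21,500 = 2.3% |
| 5 | assumed | 1/15,000 | 490/15,000 = 3.3% |
| 10 | assumed | 1/9,300 | 490/9,300 = 5.3% |

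The first half-life divides an average by an upper bound, so it is an assumption and not an estimate. Against the 1/20,000 bound, the range runs from 20,000/36,500 = 0.55 to 20,000/9,300 = 2.2 times.

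**4. Sensitivity of the test to a shift.** With no true fludarabine effect and n = 12, an assumed spurious mean difference of 0.5, 1 or 2 days would be declared significant with probability 0.12, 0.35 or 0.88 (SD of the difference 2), or 0.09, 0.20 or 0.61 (SD 2.83), against a nominal 0.05. These shifts are assumed. Nothing in the protocol links the residual levels in step 3 to a shift of any given size.

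**The case against.** The strongest reply is that the Appendix D interval is longer than the one in Section 12.1, so on that schedule the comparison is better protected than the text claims, and Section 4 already uses with-IL-2 figures. That stands. It makes this a failed justification and not evidence of material carry-over.

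A reader might infer that residual cells amount to 490/890 = 55% of the second infusion's Day 1 level. The documents do not support this. The ratio applies only to reinfusion at two weeks, which Appendix D does not schedule. It also treats an average up to Day 14 as a Day 14 value, although Section 2.4.1 notes decline by day 10.

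A reader might also infer that the comparison is shown to be biased towards fludarabine. It is not. The Section 10 endpoints are peak frequency and median survival, and no calculation shows how far a residual of a few percent would move them. The net direction is open as well: Section 2.4.1 cites counterregulation after prolonged IL-2, so an earlier IL-2 course could shorten the persistence of Infusion #2.

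The fixed order is openly declared and defensible. Section 2.5 puts fludarabine lymphopenia at about 4 to 6 weeks, so giving fludarabine first could affect the unconditioned infusion at this spacing. That justifies the order but does not make lymphodepletion the only difference.

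Handling of baseline values is often left to a statistical analysis plan, and its absence here is not the complaint. The complaint is that the protocol states a reason for needing none, and its own data contradict that reason.

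**Conclusion.** The point holds as a wrong justification and an overstated attribution. The interval, the clearance claim and the description of Infusion #1 in Section 12.1 fit a design without IL-2. They conflict with Appendix D, Section 2.6 and Section 2.4.6. Section 7.2 carries the same no-IL-2 figures.

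On the Appendix D interval, carry-over is probably small on average, at most about 1.3% to 5.3% of the Day 1 level. This rests on exponential decline from the Day 21 bound with half-lives of about 2.6 to 10 days. These are averages, so they do not exclude carry-over in patients whose cells outlast the median. The sample size, test and power are unaffected; what changes is how the paired difference may be interpreted. Lymphodepletion alone is not identified, because fludarabine and order cannot be separated in this design.

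**What to change.** - In Section 12.1, reconcile the interval and the description of Infusion #1 with Appendix D, Section 2.6 and Section 4. Reconcile the no-IL-2 figures in Section 7.2 in the same pass. The sponsor must settle which statements are intended.
- Replace the claim about two weeks with an argument from with-IL-2 data, stating that no Day 28 level is available from the earlier study.
- Add a sensitivity analysis that corrects the Infusion #2 persistence values for each patient's Day +28 pre-infusion level. Appendix D already schedules that sample. Note that subtracting a constant over-corrects later time points, because residual cells would keep declining; the analysis is therefore conservative with respect to a fludarabine effect.
- Do not exclude patients with detectable cells at Day +28. That would select on Infusion #1 persistence, the comparator outcome, and could itself inflate the paired difference.
- In Section 2.6, say that IL-2 is balanced between the infusions, but that the contrast is fludarabine together with order: a second infusion, an earlier IL-2 course and a later time.

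The cost is revised text, one extra analysis and a slightly weaker causal claim. No change to the sample size or visits is needed for the analysis.

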### 4. STUDY DESIGN

This will be a single center, phase I, open-label, nonrandomized study in 12 individuals with metastatic melanoma (Stage IV disease). Antigen-specific T cells targeting one of the A2 or A3-restricted epitopes of the melanoma-associated antigens listed in Table 1 (Appendix A ) will be generated in vitro.

Patients will receive T cell infusions according to the following schedule:

[figure not shown]

Protocol 1796.00

Antigen-specific CD8+ T cell clones will be administered at a dose of  $10^{10}$  cells/m^2 for both Infusions #1 and #2. The median survival of transferred antigen-specific CTL clones in the presence of low-dose IL-2 (250,000 U/m^2) is approximately 17 days. By the end of 21 days, the frequency of transferred CTL is < 0.1% of the total CD8+ population. Fludarabine 25 mg / m^2 will be administered intravenously daily for 5 days prior to the second infusion of antigen-specific CD8+ CTL clones which will also be administered in the presence of low-dose IL-2. Four weeks after the second infusion, patients will be re-evaluated clinically and radiographic to determine the response to therapy. Serial blood draws during this time will allow us to determine if fludarabine lymphodepletion contributed to a prolongation of the median T cell survival beyond the expected 17 days seen with low-dose IL-2 alone.

If serious toxicity related to the T cell infusions is observed following infusion of CTL clones, , a regimen of corticosteroids will be given, and no further T cell infusions will be administered to the patient.

Subjects will be carefully monitored at regular intervals for a total of approximately 9 months following the last infusion. Evaluations after this time will be carried out by the referring physician who will be asked to notify us of the patient's progress. Peripheral blood from the patient will also be drawn. Patients receiving T cells will have up to approximately 4 tablespoons of blood drawn immediately prior to each infusion, 24 hours after each infusion, and then at specified intervals for 4 weeks from the last infusion (Appendix D). Samples will be used to evaluate the duration of in vivo persistence, function and trafficking of infused T cell clones. As a secondary objective, the residual measurable disease in these patients will also be followed to assess the therapeutic efficacy, if any, of these infusions. The estimated time to completion of the study is 24 months.

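### Section 12.1 rests its no-carryover assumption on a two-week interval the schedule does not use and on clearance seen without IL-2, a regimen no longer given

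*Protocol*

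**What the plan says.** Section 12.1 compares T cell survival after Infusion #1 with survival after Infusion #2 in the same patient. It describes Infusion #1 as T cells with nothing else, and Infusion #2 as preceded by fludarabine. It then dismisses residual cells as a confounder on two grounds: the interval ("the second infusion given occurs 2 weeks after the first infusion at a time when transferred CD8 cells have disappeared from the circulation") and earlier experience ("in our previous study, transferred CD8+ T cells were undetectable at two weeks").

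Other current sections describe a different trial:

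- **Schedule.** Appendix D gives Infusion #1 on Day 0, fludarabine on Days +21 to +25, and Infusion #2 at the row labelled "Day+ 28 Pre-Infusion". Section 7.2 starts fludarabine seven days before Infusion #2.
- **IL-2.** Section 2.6 states that "a 14-day course of low-dose IL-2 following both the first and second T cell infusions will be administered".
- **Expected survival.** Section 4 looks for "prolongation of the median T cell survival beyond the expected 17 days seen with low-dose IL-2 alone". It adds: "By the end of 21 days, the frequency of transferred CTL is < 0.1% of the total CD8+ population".
- **Earlier study.** Section 2.4.6 describes "four unmodified T cell infusions three weeks apart, the 2nd, 3rd and 4th infusions being accompanied by a 14-day course of low-dose IL-2". In the infusions with IL-2 the frequency averaged 1/890 "PBMCs until Day 14 at which time, IL-2 was discontinued and T cell frequency fell to" below 1/5700 by Day 21.

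**The concern.** The primary comparison is paired, and it needs cells from Infusion #1 to be gone, or at least measured, before persistence of Infusion #2 is assessed. Section 2.6 goes further and attributes any difference in survival to lymphodepletion alone. Residual cells that the assay cannot separate from the new ones would count toward Infusion #2 and could make its persistence look longer.

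The two-week sentence is the only argument the statistical section offers against this. A median survival of about 17 days cannot be squared with cells having disappeared by day 14. The paragraph appears to have been carried over unchanged when IL-2 was added. An analyst working from Section 12.1 alone would take the wrong interval, the wrong clearance data and the wrong description of the control infusion.

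**Working it through.** **1. Interval.** Appendix D: Infusion #2 on Day 28. Section 7.2: fludarabine starts at Day -7 relative to Infusion #2, and 28 - 7 = 21, which matches Appendix D. Section 12.1: 14 days. Two sections agree and Section 12.1 stands alone.

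**2. Which data support clearance at two weeks?** All inputs are from Section 2.4.6, as frequency among PBMCs.

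| | Without IL-2 (22 infusions) | With IL-2 (12 infusions) |
|---|---|---|
| Day 1 | 1/480 | 1/490 |
| To Day 14 | 1/1500 by Day 7; below 1/20,000 by Day 14 | average 1/890 until Day 14 |
| Day 21 | not given | below 1/5700 |
| Median survival | 6.56 days | 16.78 days |

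Relative to Day 1:

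- without IL-2, Day 14: below 480/20,000 = 2.4%
- with IL-2, average until Day 14: 490/890 = 55%
- with IL-2, Day 21: below 490/5700 = 8.6%

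The 55% is an average up to Day 14, not the Day 14 level. Section 2.4.1 notes that decline began by day 10. Even so, only the left column fits a claim that cells were undetectable at two weeks, and the current regimen belongs to the right column. The Day 21 bound with IL-2 is 20,000/5700 = 3.5 times the 1/20,000 level.

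**3. What is known at Day +28?** The protocol gives no Day 28 frequency with IL-2. For scale only, assume that Infusion #2 also reaches 1/490 on Day 1, that the assay cannot tell the two infusions apart, and that fludarabine does not change the frequency per PBMC. The residual share of the Infusion #2 Day 1 signal is then (1/r) / (1/r + 1/490) = 490/(490 + r).

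- No further fall after Day 21 (r above 5700): below 490/6190 = 7.9%.
- Same rate of fall as from 1/890 to 1/5700, a factor of 5700/890 = 6.4 per week, treating 1/890 as the Day 14 value and 1/5700 as exact: r = 5700 x 6.4, about 36,500, giving 490/36,990 = 1.3%.

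These figures illustrate scale. They are not estimates, and neither is expressed in days of T cell survival, which is the endpoint.

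**4. Stated power.** One-sample t-test on 12 paired differences, difference 4 days, SD 2 days, two-sided .05:

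- noncentrality (4/2) x √12 = 6.93 on 11 df: power above .999
- if 2 days is instead the SD per infusion with zero correlation, the SD of the difference is 2 x √2 = 2.83: power .993

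Both agree with the stated figure of about 99%. The interval between infusions is not an input, so correcting it leaves the power unchanged.

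**The case against.** The best defence is that this is stale text with no effect on the trial. The real gap is longer than the one stated, so the error makes the design look weaker than it is. Section 4 already carries the with-IL-2 figures, and fludarabine starts on the day to which they refer. The pre-infusion research draw on Day +28 is already scheduled. The protocol also uses clone-specific PCR for other purposes (Sections 7.4.5 and 8.2.3). That could separate the two infusions if different clones are used, which the documents do not say.

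All of that stands, and it limits the consequence. It does not repair the argument. Section 4 does not discuss carryover, and Section 12.1 does not cite Section 4. A frequency below 0.1% of CD8+ cells at Day 21 is also not the same as undetectable.

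A reader might infer three stronger conclusions, and the documents support none of them:

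- **The trial is confounded by carryover.** No Day 28 level is reported, and the with-IL-2 data show a steep fall by Day 21. Treating the 17-day median as an exponential half-life would leave 0.5^(28/17) = 32% at Day 28. The same model predicts 0.5^(21/17) = 42% at Day 21, against the reported value below 8.6%, so it does not fit.
- **The schedule is too short.** Appendix D allows four weeks. The earlier study spaced its infusions three weeks apart.
- **The sample size is wrong.** The stated power reproduces on its own inputs.

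**Conclusion.** The point holds as a defect in the justification of the primary comparison. Section 12.1 states 14 days where the schedule has 28. It relies on clearance below 2.4% of the Day 1 level, seen without IL-2, where the with-IL-2 data show an average of 55% until Day 14 and below 8.6% by Day 21. Its description of Infusion #1 also omits the IL-2. As written, the statement that residual cells will not confound is unsupported for the regimen being given.

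It is not shown to be false. Under the assumptions above, residual cells at Day +28 would be below about 8% of the Infusion #2 Day 1 signal, and possibly near 1%. Design, schedule, sample size and power stay as they are. It goes beyond a clerical slip because no other carryover argument stands behind the primary endpoint, and valid support is available elsewhere in the protocol. It should be corrected.

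**What to change.** In Section 12.1:

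1. State that Infusion #2 is given on Day +28, after fludarabine on Days +21 to +25.
2. Define the contrast as T cells plus IL-2 (Infusion #1) versus fludarabine, T cells plus IL-2 (Infusion #2), and drop the description of Infusion #1 as unaccompanied.
3. Replace the two-week clearance claim with the with-IL-2 data from Sections 2.4.6 and 4.
4. State that the Day +28 pre-infusion research sample will be used to measure residual Infusion #1 cells, and that any found will be accounted for in the Infusion #2 persistence analysis.
5. Say whether the four patients treated without IL-2 (Section 2.6) count toward the 12. If they do, report their pairs separately.

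The cost is wording. No visit, sample or patient is added. If four pairs are set apart, the remaining eight have noncentrality (4/2) x √8 = 5.66 and power of about .998 at Section 12.1's own values. If 2 days is the SD per infusion with zero correlation, the power is .927.
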